**Methods:**

The study is a multi-centred, two-arm clustered randomised controlled trial. Organisations will be randomly allocated to the control or intervention (estimated sample size 800 recipients). The intervention is the standard MHFA intervention provided by Mental Health First Aid England (MHFAE). The control condition will be organisations having a brief consultation from MHFAE on promoting mental health and well-being in the workplace. The primary outcome is health seeking behaviour, measured using the Actual Help Seeking Questionnaire, at 6 months’ follow-up. Data collection will be undertaken at baseline (T0), post-intervention—up to 3 months (T1), at 6 months (T2), 12 months (T3) and 24 months (T4). The primary analysis will be conducted on those participants who receive MHFA, a per protocol analysis.

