### Outcomes {12}

#### Primary outcome

The primary outcome is Employees’ help-seeking behaviour at 6 months measured by the Actual Help-Seeking Questionnaire [AHSQ] [11]. The AHSQ measures help-seeking behaviour in the 2 weeks preceding the assessment and will be assessed at baseline, 6, 12 and 24 months. Help-seeking behaviour is determined by listing the number of help sources, the type of help sought and whether help seeking has occurred during the allocated time period.

The primary analysis will be conducted on those participants who receive MHFA and therefore is a per protocol analysis. Further analyses will examine the impact of the intervention at the organisational level using an intention-to-treat analysis with all respondents included.

As this is a small non-random subsample of randomised participants, it is recognised that this analysis will be vulnerable to selection bias and uncontrolled confounding. For this reason, a range of baseline participant characteristics will be included in the primary analysis to mitigate these limitations.

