### Participant timeline {13}

#### Sample size {14}

The sample size calculation is based on a simplification of the proposed analysis model (Fig. 1).

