**Fig. 1 Fig1:**
[figure not shown]
CONSORT trial flow diagram

To be able to detect a change of two additional help seeking resources [11], with 80% power at the 0.05 alpha level, assuming that the mean in the control group is 1 and in the intervention group 3 with a common standard deviation of 8, 506 participants are required, increasing to 596 allowing for 15% attrition at 6 months. Pilot data indicates a response rate of 40% across organisations and an average cluster size of 72 employees (calculated from organisations currently signed up) therefore approximately 29 employees per organisation (cluster size). With 24 clusters, 12 organisations per condition, and assuming an intraclass correlation coefficient (ICC) equal to 0.01 (ICC’s are lower for participant outcomes as opposed to process variables, when cluster size is large and when estimates are adjusted by participant baseline characteristics [21]), a minimum target sample size is 763, rounded up to 800, 400 per condition

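### The 80% power is calculated for all responding employees, but the primary analysis uses only the small subset who receive MHFA, so the primary analysis does not have that power

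*Protocol article*

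**What the plan says.** The section Sample size {14} introduces the calculation with "The sample size calculation is based on a simplification of the proposed analysis model". It asks for detection of two additional help sources "with 80% power at the 0.05 alpha level". The effect assumption on which this rests is worded "assuming that the mean in the control group is 1 and in the intervention group 3 with a common standard deviation of 8". Before any allowance for clustering, the protocol concludes that "506 participants are required, increasing to 596 allowing for 15% attrition at 6 months". Clustering is then allowed for: "Pilot data indicates a response rate of 40% across organisations and an average cluster size of 72 employees", which the protocol turns into about 29 employees per organisation, with 12 organisations per arm and an ICC of 0.01. The result is "a minimum target sample size is 763, rounded up to 800, 400 per condition".

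The Primary outcome section (Outcomes {12}) and the abstract both restrict the primary analysis to participants who receive MHFA and call it per protocol. The Primary outcome section adds "As this is a small non-random subsample of randomised participants" and warns of selection bias and confounding. It lists the intention-to-treat analysis of all respondents under further analyses.

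The abstract (Methods) gives the sample size as "estimated sample size 800 recipients". The comparator section {6b} has control organisations agree not to introduce the 2-day MHFA training during the study.

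**The concern.** The calculation and the primary analysis concern different groups. The first counts respondents; the second keeps only those who received MHFA. No step links the two by a recipient share, and no power is given for the subset.

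Two misreadings follow. A null primary result would be taken as coming from a trial with 80% power, although the test actually run had much less. A reader of the abstract would also believe that 800 recipients are analysed, when 400 of them are controls and, if the subsample is small as the protocol says, most of the other 400 are not recipients either.

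The effect assumption has the same problem. A mean of 3 is assumed for the intervention arm without saying whether it describes recipients or all employees. If only recipients change, the whole-arm difference shrinks in proportion to their share.

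**Working it through.** **Inputs from Sample size {14}:** difference 3 − 1 = 2; SD 8; alpha 0.05 (sidedness not stated; two-sided reproduces the figure); power 80%; attrition 15%; 12 organisations per arm; 40% of 72 ≈ 29 respondents per organisation; ICC 0.01; 400 per arm.

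**Assumption, not in the documents:** f, the share of intervention-arm respondents who receive MHFA.

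**Step 1: the protocol's own figures.**
- Two-sample t-test, standardised difference 2/8 = 0.25: 253 per arm, 506 in total.
- Attrition: 506/0.85 = 595.3, so 596.
- Design effect: 1 + (29 − 1) × 0.01 = 1.28; 596 × 1.28 = 762.9, so 763.

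All three reproduce. The chain is complete without a recipient factor, so none is hidden in it.

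**Step 2: power of the recipient analysis.** After attrition there are 400 × 0.85 = 340 controls and 340f recipients.

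SE = 8 × √(DEc/340 + DEr/(340f)), with DE = 1 + (m − 1) × 0.01, m = 340/12 = 28.3 for controls (DEc = 1.273) and m = 340f/12 for recipients. Power = Φ(2/SE − 1.96). The difference detectable with 80% power is 2.80 × SE.

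For f = 20%: 68 recipients, m = 5.67, DEr = 1.047, SE = 8 × √(1.273/340 + 1.047/68) = 1.107, power = Φ(−0.153) = 44%, detectable difference 3.1.

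| f | Recipients analysed | SE | Power | Detectable difference |
|---|---|---|---|---|
| 100% | 340 | 0.692 | 82% | 1.9 |
| 75% | 255 | 0.736 | 78% | 2.1 |
| 50% | 170 | 0.816 | 69% | 2.3 |
| 30% | 102 | 0.956 | 55% | 2.7 |
| 20% | 68 | 1.107 | 44% | 3.1 |
| 10% | 34 | 1.469 | 27% | 4.1 |
| 5% | 17 | 2.005 | 17% | 5.6 |

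Power reaches 80% only at f of about 86%. If recipients were compared with an equal-sized control subset, power would be 58%, 41%, 30% and 17% at f = 50%, 30%, 20% and 10%. Clustering is not the cause: with ICC 0, f = 20% gives 47%.

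**Step 3: the all-respondent analysis if only recipients gain 2 sources.** The difference becomes 2f and SE = 8 × √(2 × 1.273/340) = 0.692. Two-sided power is 9% at f = 20% (8% without the opposite tail), 14% at 30% and 30% at 50%. This assumes no gain at all in non-recipients.

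**Step 4: a check on the base case.** The stated clusters supply 24 × 29 = 696 respondents, fewer than 763 or 800. The 340 per arm used above is therefore on the generous side; with 348 recruited per arm, power at f = 20% is 40%.

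**The case against.** **The arithmetic is right.** It is, and this stands. The fault is that a correct calculation is attached to the wrong analysis population.

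**The primary population is itself unclear.** The statistical methods section {20a} compares groups by intervention status without naming recipients, and {20b} enters the nature and frequency of MHFA experienced as a covariate, which fits a data set that includes non-recipients at least as well. If the primary analysis were reconciled to all respondents, the recipient power would no longer be the primary analysis's problem. But the abstract and the Primary outcome section both name recipients, and nothing in the protocol resolves the matter the other way. An all-respondent primary analysis would then rest on a whole-arm difference of 2, with the dilution shown in Step 3.

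**The stated model may be more precise than a follow-up comparison.** This is fair, and the power figures are illustrative for that reason. With an assumed baseline-to-6-month correlation of 0.6, power at f = 20% becomes 52% for a change-type contrast (the time-by-group interaction in the protocol) and 62% with baseline adjustment; at f = 50% the figures are 78% and 87%. With a correlation of 0.3 the change contrast is worse, 33% at f = 20%. At f = 20% the change contrast would need a correlation of about 0.79 to reach 80%. The protocol states no correlation. Calling the calculation a simplification of the model does not cover a change of population.

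**Non-recipients may benefit.** Raising awareness is part of the intervention. If non-recipients gained one source, the whole-arm difference at f = 20% would be 0.2 × 2 + 0.8 × 1 = 1.2 and power 41%, not 9%. So Step 3 is a scenario, not an estimate, and indirect benefit does nothing for the recipient analysis.

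**The share is unknown.** True. The size of the loss cannot be fixed from the documents, and that most intervention-arm respondents are not recipients is inferred from the protocol's word for the subsample. The recommended ratio of one trained employee per ten concerns first aiders, not recipients, and does not supply f.

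**Conclusion.** The concern holds. The 80% power, the 763 and the 800 describe a comparison of all respondents, which the protocol does not make primary. For the stated primary analysis, with the protocol's own planning values and an unadjusted comparison, power is about 27% to 55% for recipient shares of 10% to 30%, and 69% at 50%. The share of about 86% needed for 80% cannot be squared with a subsample the protocol calls small. The exact loss depends on the assumed share, on any gain from baseline adjustment, and on which controls are compared, but none of these restores 80% at a small share without an unstated high baseline correlation. The abstract's count of recipients is wrong whatever the share, because 400 of the 800 belong to control organisations.

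**What to change.** - In Sample size {14}, state that the 80% applies to the comparison of all respondents, and only if the difference of 2 holds across the whole intervention arm.
- Add a table of power, or of the difference detectable with 80% power, for the recipient analysis over a range of recipient shares. Use the pilot's share if it was measured there; the protocol reports only a response rate from the pilot, so otherwise label the range as assumed. Name the control group used for the comparison.
- State whether the difference of 2 is meant for recipients or for all employees.
- In the abstract, replace the count of recipients with 800 responding employees.

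The cost is a set of restated figures, less favourable than those now claimed. The correction needs no extra enrolment, but it does not add power: the recipient analysis would be reported with the precision it has. Powering that analysis at 80% would be a different undertaking. At f = 20% it needs 808 analysed controls and about 162 recipients, which is 2 × 808/0.85 ≈ 1,902 respondents, or 1,902/29 ≈ 66 organisations. At f = 10% it needs 2 × 1,430/0.85 ≈ 3,365 respondents, about 116 organisations.

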#### Recruitment {15}

Organisations expressing an interest (directly to MHFAE) in undertaking MHFA training, who are willing to take part in the study, will be asked to contact [name] (GD: Centre for Mental Health) for detailed information about the study. Then, if willing to take part, the Senior Manager will sign a written agreement and their contact details will be sent to the research team. The research team will email the Senior Manager, detailing what will happen next, asking for company demographics (see secondary outcomes below) and requesting they send a standard email to ALL employees providing information about the study with a link to the survey for completion of baseline measures. One, 2 and 3 weeks later, the research team will send the Senior Manager another standard email, to be sent to ALL employees, as a gentle reminder to complete the survey.

At each follow-up, the research team will send participants (Senior Managers) up to four weekly email reminders to remind employees to complete measures.

**Assignment of interventions: allocation**

**Sequence generation {16a}**

**Concealment mechanism {16b}**

**Implementation {16c}**

#### Randomisation

The unit of randomisation is organisation, and randomisation of organisations will be stratified by size of organisation, with three strata being defined [22], small (< 50 employees), medium (50–249 employees) and large (> 250 employees). The randomisation schedule will be generated by GD using Random.org (https://www.random.org/randomness/) and allocation assigned to an organisation after completion of baseline measures.

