### Statistical methods

#### Statistical methods for primary and secondary outcomes {20a}

All outcomes will be described with the appropriate descriptive statistics: mean and standard deviation for continuous outcomes (or medians and interquartile range for skewed data) and counts and percentages for dichotomous and categorical outcomes.

The analysis of the primary outcome will estimate the mean difference (with 95% confidence intervals) in the Actual Help-Seeking score at 6-month follow-up between the intervention (MHFA) and standard care groups using a mixed effects repeated measures model (which assumes incomplete outcome data to be missing at random). The model will incorporate demographic and other baseline covariates as fixed effects. The dependent variable will be the count of help sources on the Actual Help-Seeking questionnaire. The independent variable will be ‘time point’. The effect size of the intervention will be estimated as the exponentiated coefficient for the interaction term between time point (baseline versus 6-month follow-up) and intervention status (MHFA versus control group). A random effect of participant will be included in the model to adjust for the repeated measures on participants. ‘Employing organisation’ will be included as a higher level random effect (with participants nested in employers). Statistical significance will be at the 5% level.

Secondary outcomes will be analysed using an appropriate generalised linear model, for example binary logistic regression for dichotomous outcomes and ordinal logistic regression for ordered categorical outcomes. All models will be adjusted for employing organisation and baseline score (where applicable).

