### Methods for additional analyses (e.g. subgroup analyses) {20b}

Age, gender, level of education, ethnicity, nature and frequency of MHFA interventions directly experienced will be included in the primary analysis as covariates.

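### Organisation size stratifies the randomisation but is named in no analysis model, and an organisation of exactly 250 employees fits no stratum

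*Protocol article*

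**What the plan says.** Under Randomisation, the protocol article makes the organisation the unit of randomisation and says that "randomisation of organisations will be stratified by size of organisation, with three strata being defined": "small (< 50 employees), medium (50–249 employees) and large (> 250 employees".

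Under Statistical methods {20a}, the primary model is a mixed-effects repeated-measures model. The treatment effect is the interaction of time point (baseline versus 6 months) with arm, and there are random effects for participant and for employing organisation. On fixed effects it says: "The model will incorporate demographic and other baseline covariates as fixed effects". The section on additional analyses {20b} then names them: "Age, gender, level of education, ethnicity, nature and frequency of MHFA interventions directly experienced will be included in the primary analysis as covariates". Every variable in that list belongs to the participant. For secondary outcomes, section {20a} says: "All models will be adjusted for employing organisation and baseline score (where applicable".

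The Primary outcome section makes the main analysis per protocol, in those who receive MHFA, and adds an intention-to-treat analysis of all respondents. It concedes that the per-protocol group is a small, non-random part of those randomised, and offers participant baseline characteristics as the remedy.

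**The concern.** Stratified randomisation balances the arms on the stratifier, so variation due to that factor no longer contributes to the arm contrast. A model that omits the factor still counts that variation as error between organisations. Its standard errors then describe a less precise design than the one used: intervals are too wide and tests are conservative. A random intercept for organisation does not repair this, because its variance includes the part due to size.

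With only 24 organisations, the between-organisation component matters. What is at stake is some efficiency in the randomised comparisons and, in the per-protocol analysis, possible imbalance on a factor that could plausibly affect who receives MHFA.

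The gap at 250 is a different kind of problem. An allocation rule has to place every eligible organisation in exactly one stratum.

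**Working it through.** **The plan's own figure.** Inputs from the Sample size section: difference 2, SD 8, 80% power, alpha 0.05, attrition 15%, about 29 respondents per organisation (72 × 40% = 28.8), 24 organisations, ICC 0.01.
- A two-sided t-test needs 253 per arm, 506 in total, as stated.
- 506 / (1 − 0.15) = 595.3, so 596, as stated.
- Design effect 1 + (29 − 1) × 0.01 = 1.28, and 596 × 1.28 = 762.9, so 763, as stated.

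This chain reproduces and does not depend on the present point.

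**One time point, all respondents.** Let s be the share of between-organisation variance explained by size. The documents give no value for s, so it is an assumption. With balanced strata, a model that includes size has design effect 1 + 28 × 0.01 × (1 − s).

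| s | Design effect | SE relative to omitting size |
|---|---|---|
| 0% | 1.28 | 1.000 |
| 25% | 1.21 | √(1.21/1.28) = 0.972 |
| 50% | 1.14 | √(1.14/1.28) = 0.944 |

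The standard error therefore falls by nothing, about 3% and about 6%.

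A simulation of organisation means agrees (24 organisations of 29, SD 8, ICC 0.01, eight organisations per stratum split 4:4, 20,000 runs). At s = 0, 25% and 50%:
- type I error without size is 0.048, 0.043 and 0.039, and stays near 0.05 with size;
- power without size is 0.79, 0.80 and 0.81, and with size 0.79, 0.82 and 0.84.

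**The primary model.** Its effect is a time-by-arm interaction, which is essentially a difference in change. A size effect that is the same at baseline and at 6 months largely cancels from it. I computed the generalised least squares standard error of the interaction for the same layout with two time points. Assumptions: participant variance share 0.3 or 0.5, follow-up loss 0 or 15%, variance components known, s = 50%.
- With an arm main effect in the model, the ratio of standard errors (size included to size omitted) is 1.000 in every scenario.
- With baseline means constrained equal, so no arm main effect, the ratio runs from 0.976 to 0.987, a fall of 1.3% to 2.4%.
- Adding a size-by-time term as well leaves these ratios unchanged when strata are balanced.

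**The stratum limits.** Applying the three rules as written:

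| Employees | Stratum |
|---|---|
| 49 | small |
| 50 | medium |
| 249 | medium |
| 250 | none |
| 251 | large |

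**The case against.** The strongest reply is that nothing in the article excludes size. The phrase about other baseline covariates in section {20a} is open, company demographics are requested from each organisation under Recruitment, and a separate analysis plan could name the stratifier. That stands in part: it would be too strong to say that the plan rules size out. But the article does not leave the matter entirely open. It names the primary covariates and the secondary adjustment set, and the only factor used to stratify the randomisation is in neither.

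A reader might go further and infer that the primary interval will be about 6% too wide, or that including size would cut the required total from 763 to about 680 (596 × 1.14 = 679). The documents do not support either inference. Both figures come from a comparison of arms at a single time point among all randomised respondents, whereas the planned primary effect is a time-by-arm interaction in a per-protocol subset. They also rest on a 50% share for which the documents offer no evidence.

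The argument that stratification has already removed size from the contrast is weaker still in the per-protocol group. Balance among randomised organisations does not guarantee balance among those who receive MHFA. This limits the precision argument there, but it is itself a reason to adjust for size.

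Finally, the gap at 250 is very likely a slip, and with an average of 72 employees per organisation it may never arise. That is fair, and it is a small point.

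**Conclusion.** The omission is real, and its effect is modest. In intention-to-treat or secondary models comparing arms at one time point, standard errors are too large by an amount that depends on how well size predicts outcome: nothing, about 3%, or about 6% at shares of 0, 25% and 50%. This assumes ICC 0.01, 29 respondents per organisation, balanced strata and a continuous outcome. The error is on the conservative side and does not bias the randomised comparison.

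For the primary interaction, a size main effect changes the standard error by about 0 to 2% at the 50% share. Size matters there chiefly because the per-protocol subset may differ in size mix between arms. If change in help-seeking varies with size, only a size-by-time term adjusts for that.

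The stated sample size is unaffected. The stratum limits contain a literal gap at 250 employees, small in practice but simple to close.

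**What to change.** - Add the three-level size stratum, as used at randomisation, as a fixed effect in the primary, intention-to-treat and secondary models.
- In the repeated-measures primary model, also include size by time point, so that the adjustment reaches the contrast being estimated.
- Define the large stratum as 250 employees or more. If an organisation of exactly 250 has already been randomised, record the stratum in which it was placed and analyse it there.

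The statistical cost is about two of the 22 organisation-level degrees of freedom (24 organisations less two arms). Stratum membership has to be known for every organisation before allocation, so no new data are needed. The administrative cost is a short amendment: recruitment was under way at this protocol version, and the article says that the ethics committee must approve important changes.

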### Eligibility criteria {10}

Inclusion criteria are as follows: organisations expressing an interest (directly to MHFAE) in undertaking MHFA training, who have not undertaken this training previously and who agree to participate and are able to provide data on sickness absenteeism, presenteeism and other productivity data. For the purposes of this study, participants will be all employees working in each organisation who provide help-seeking outcome data.

Exclusion criteria are as follows: organisations who have already introduced MHFA across all sites and departments; those who decline to participate in adopting MHFA training; and organisations, employees, mental health first-aiders and recipients who participated in the pilot study.

The intervention will be delivered by qualified MHFAE trainers.

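### The minimum of 763 assumes 24 organisations of equal size, although the plan admits organisations from under 50 to over 250 employees; 80% power from 800 is therefore not assured.

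*Protocol article*

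**What the plan says.** Sample size {14} plans a two-group comparison "with 80% power at the 0.05 alpha level". The effect to be detected is set by "assuming that the mean in the control group is 1 and in the intervention group 3 with a common standard deviation of 8". From these inputs the section concludes that "506 participants are required, increasing to 596 allowing for 15% attrition at 6 months". For clustering it reports that "Pilot data indicates a response rate of 40% across organisations and an average cluster size of 72 employees", the mean coming from the organisations enrolled so far, and "therefore approximately 29 employees per organisation (cluster size"). The design is then described by "With 24 clusters, 12 organisations per condition"; at an ICC of 0.01 the minimum is given as 763 and rounded up to 800.

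Three other places bear on how unequal the clusters will be:

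- Eligibility criteria {10} sets no lower or upper limit on organisation size and states that "participants will be all employees working in each organisation who provide help-seeking outcome data".
- Recruitment {15} has the survey link sent to every employee, so respondents per organisation follow organisation size, with no cap and no sampling.
- Randomisation stratifies by size, with "three strata being defined [22], small (< 50 employees), medium (50–249 employees) and large (> 250 employees").

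**The concern.** The design provides for organisations of very different size, while the sample size calculation uses only their mean. For a fixed mean, variation in cluster size lowers the information in a cluster trial: the larger organisations supply many respondents, each of whom adds less independent information. A design effect built on the mean alone is the best case.

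If sizes vary substantially, the stated minimum is too low and the power of 800 is below the stated 80%. A reader of a null result would then credit the trial with more power than it had.

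**Working it through.** **Inputs from the Protocol article, Sample size {14}:** difference 2, SD 8, alpha 0.05 (taken as two-sided, which reproduces the figure), power 80%, attrition 15%, mean 72 employees, response 40%, 24 organisations, ICC 0.01.

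**Reproducing the plan's figure**

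1. Two-sample t-test, standardised difference 2/8 = 0.25: 253 per arm, 506 in total.
2. Attrition: 506 / 0.85 = 595.3, so 596.
3. Respondents per organisation: 72 × 0.40 = 28.8, so 29.
4. Design effect: 1 + (29 − 1) × 0.01 = 1.28.
5. 596 × 1.28 = 762.9, so 763.

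Every step reproduces. Step 4 is the equal-cluster form and contains no term for variation in size.

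**Allowing for unequal sizes**

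Design effect: DE = 1 + ((1 + CV²) × 29 − 1) × 0.01.
Required number: 596 × DE.
Power of 800: 800 × 0.85 = 680 analysed, effective number 680 / DE, power = Φ(0.25 × √(680 / (4 × DE)) − 1.96).

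The CV is not in the document, so each row is an assumption.

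| CV | DE | Required number | Power of 800 |
|---|---|---|---|
| 0 | 1.280 | 763 | 82.2% |
| 0.4 | 1.326 | 791 | 80.8% |
| 0.5 | 1.353 | 807 | 80.0% |
| 0.75 | 1.443 | about 860 | 77.4% |
| 1.0 | 1.570 | 936 | 73.9% |

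For 763, any CV above zero makes 596 × DE exceed 763. The margin is slightly wider in terms of power: because of rounding, 763 computes to 80.3% at CV 0 and stays at 80% up to a CV of about 0.2.

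For 800, the break-even CV is about 0.50 by the power formula. By the required number it is slightly lower: 800 / 596 = 1.342, so (1 + CV²) × 29 = 35.2 and CV = 0.46.

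**What size mix gives a CV of 0.75?** Take 24 organisations with mean 72, two of them with 251 employees (one per arm) and the rest equal. The other 22 have (24 × 72 − 502) / 22 = 55.7 employees each. The variance is (2 × 179² + 22 × 16.3²) / 24, about 2,900; the SD is about 54 and the CV 54 / 72 = 0.75. This is the mildest mix of mean 72 with a large organisation in each arm.

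**Check against the planned analysis.** The mixed model in Statistical methods {20a} gives large clusters less weight per person. Its effective number is the sum over organisations of m / (1 + (m − 1) × 0.01), with the 680 analysed shared out by size (28.3 per organisation on average).

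| Assumed mix (mean 72) | CV | Power, CV formula | Power, mixed-model weighting |
|---|---|---|---|
| 24 equal | 0 | 82.4% | 82.4% |
| 1 of 251, 23 equal | 0.52 | 80.1% | 81.2% |
| 2 of 251, 22 equal | 0.75 | 77.7% | 79.7% |
| 12 of 28, 10 of 89, 2 of 251 | 0.85 | 76.4% | 78.3% |

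These powers differ slightly from the first table because 28.3 is used in place of 29. Variation lowers power under either weighting.

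**Sensitivity to the mean cluster size.** If cluster size is counted after attrition (29 × 0.85 = 24.65), the break-even CV for 800 rises to 0.69. If 800 recruits come from exactly 24 organisations (800 / 24 = 33.3 each), it falls to about 0.30.

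**The case against.** **No size distribution is given.** A reader might infer that 800 employees do not give 80% power. The document does not support that. It reports a mean only, and mixes that span two strata can keep the target: 8 organisations each of 35, 65 and 116 employees (CV 0.46) give 80.6%. This objection stands, and it limits the point to power that is not assured.

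**Strata are not recruits.** Defining a band above 250 does not show that such an organisation has joined, still less one in each arm. It is tempting to say that the strata force strong variation, but that holds only if the large band is filled. Wider mixes with much lower power can be constructed, but nothing in the document points to them.

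**The formula is conservative for this analysis.** Mixed-model weighting recovers part of the loss, and in the mildest two-large mix it leaves power only 0.3 points short. This stands and the size is stated accordingly.

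**The ICC matters more.** The plan itself notes that ICCs tend to be lower in large clusters. At 0.005 the two-of-251 mix has about 84% power; at 0.02 even equal clusters have about 75%. So figures such as 860 are illustrations under the plan's ICC and not precise requirements. This does not excuse omitting the CV at the ICC the plan chose.

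**The primary analysis is per protocol.** Outcomes {12} restricts it to those who receive MHFA, so none of these powers describes that comparison. That is true, but it is equally true of the plan's own 763 and 80%. The point concerns that stated calculation, which the plan itself calls a simplification.

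**Conclusion.** The point holds in conditional form. The arithmetic from 506 to 763 is correct, but the last step assumes equal clusters, which the plan's open eligibility and size strata contradict. By the standard formula, 763 is too low as the minimum with any variation in size. The 800 covers a CV up to about 0.5 and is not assured to give 80% beyond that.

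At an assumed CV of 0.75, about 860 would be needed and 800 gives about 77% (just under 80% with mixed-model weighting). At an assumed CV of 1.0, about 936 would be needed and 800 gives about 74%. These figures rest on an ICC of 0.01, a 40% response in every organisation, a mean of 29 respondents, 15% attrition and the normal approximation. Whether a shortfall exists depends on a CV that the document does not report.

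**What to change.** In Sample size {14}, replace the factor 1.28 with 1 + ((1 + CV²) × 29 − 1) × 0.01, using the CV of employee numbers among the organisations already signed up. State that CV, and give either the required number or the power that 800 provides. If the CV proves to be below about 0.5, the same sentence confirms that 800 is sufficient.

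The cost is one recalculation from the list that already produced the mean of 72, plus one sentence. No change to recruitment is needed, because reporting the power of 800 is enough. The downside is that the stated figure may become less favourable.
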